## Abstract

**Background:**

Long term care (LTC) facilities provide health services and assist residents with daily care. At times residents may require transfer to emergency departments (ED), depending on the severity of their change in health status, their goals of care, and the ability of the facility to care for medically unstable residents. However, many transfers from LTC to ED are unnecessary, and expose residents to discontinuity in care and iatrogenic harms. This knowledge translation project aims to implement a standardized LTC-ED care and referral pathway for LTC facilities seeking transfer to ED, which optimizes the use of resources both within the LTC facility and surrounding community.

**Methods/design:**

We will use a quasi-experimental randomized stepped-wedge design in the implementation and evaluation of the pathway within the Calgary zone of Alberta Health Services (AHS), Canada. Specifically, the intervention will be implemented in 38 LTC facilities. The intervention will involve a standardized LTC-ED care and referral pathway, along with targeted INTERACT® tools. The implementation strategies will be adapted to the local context of each facility and to address potential implementation barriers identified through a staff completed barriers assessment tool. The evaluation will use a mixed-methods approach. The primary outcome will be any change in the rate of transfers to ED from LTC facilities adjusted by resident-days. Secondary outcomes will include a post-implementation qualitative assessment of the pathway. Comparative cost-analysis will be undertaken from the perspective of publicly funded health care.

**Discussion:**

This study will integrate current resources in the LTC-ED pathway in a manner that will better coordinate and optimize the care for LTC residents experiencing an acute change in health status.

**Supplementary Information:**

The online version contains supplementary material available at 10.1186/s12913-020-05919-7.

## Background

With more than five million Canadians over the age of 65, the demand for Long Term Care (LTC) facilities is projected to increase [1]. Currently, 7 % of seniors aged 65 and older reside in LTC or residences for senior citizens [2]. LTC facilities provide health services, personal care, and cater to the daily living needs of residents requiring assistance with care [3]. Most residents of LTC facilities are frail with end-stage chronic diseases, and therefore are vulnerable to conditions such as fall related injuries, pneumonia, urinary tract infections, congestive heart failure, and other conditions that may require medical care [4]. For some residents, transfer to emergency departments (ED) may be required, depending on the severity of the condition and the goals of care of the resident. However, many transfers from LTC to the ED are unnecessary and can increase the demand placed on ambulance transport services and ED resources. Additionally, LTC residents transferred from LTC to ED can experience discontinuity in care, prolonged wait times in the ED and exposure to iatrogenic harms, all of which can result in cognitive and functional decline [5, 6]. Furthermore, with the current coronavirus pandemic reducing transfers to the ED from LTC facilities may reduce the strain on the current health care system and reduce the risk of exposure of vulnerable seniors to the virus upon transfer.

When a transfer to the ED is indicated, there is often poor and inconsistent communication between LTC and ED staff. The literature suggests that the two main issues with transfers between LTC and the ED are related to the fact that the ED does not ask for specific information from LTC facilities, along with limited motivation and ability of LTC to support additional communication processes [7]. This can lead to a lack of understanding of a patient’s baseline functional and cognitive abilities, poor problem description and patient management, inefficient resource utilization, and patient and family dissatisfaction in the transfer process, all contributing to poor patient outcomes [8, 9]. Patient centered care (PCC) therefore becomes fundamental in achieving better outcomes for LTC residents. PCC should incorporate the patients’ reason for seeing the health practitioner, their requirement for information that pertains to their health, a holistic understanding of the patients’ life circumstances that considers their physical, emotional, and social context. Furthermore, PCC seeks to find common definitions of the patients’ health problem and management strategies that are tailored to the patients’ needs. PCC should also increase compliance to disease prevention and health promotion by the patient, and promote a mutually beneficial relationship between the patient and the health practitioner [10, 11].

Evaluating and managing acute conditions at LTC facilities may mitigate against the negative impact transfers have on LTC residents and their families, as well as better optimize health care resources. A recent study found that residents and their families were very satisfied with receiving acute care within LTC facilities through community paramedicine interventions, thus avoiding transfers to ED, as they felt that residents could be better cared for at LTC facilities [12]. Given the patient and health system challenges associated with LTC to ED transfers, seeking innovative ways to streamline the transfer process may help improve patient outcomes and decrease the system inefficiencies currently associated with transfers.

### Aim and objective

The aim of this study is to improve the care provided to LTC residents who develop an acute change in health status, using a patient-centered approach that requires the patients’ participation, involvement, enhances the relationship between the patient and health practitioners, and provides treatment in the most appropriate location [11]. We aim to optimize, standardize, and evaluate the processes followed when considering transfer of residents from LTC to an ED. Specifically, the objective of this research is to implement and evaluate an evidence-informed standardized care pathway for the care of LTC residents experiencing an acute change in health status**.**

## Methods

### Study design

This is an implementation trial which will follow a Hybrid III strategy in which we are testing an implementation intervention while observing and gathering information on the clinical intervention and related outcomes. A Hybrid III strategy is useful when there is face validity for the implementation interventions that would likely be generalizable to a new setting; there is a low risk of the implemented interventions negatively impacting current practices; there is endorsement or actual mandates to the adoption of the intervention; the implementation intervention should be testable in the context of the study [13]. We will use a quasi-experimental randomized stepped-wedge design in the implementation and evaluation of the pathway (i.e., intervention) within the Alberta Health Services (AHS) Calgary zone, Alberta, Canada (Fig. 1).

**Fig. 1 Fig1:**
[figure not shown]
Implementation of a stepped wedge design

By the end of the study, all 38 participating LTC facilities will have received the intervention. However, the order in which facilities receive the intervention will be determined at random [14]. A stepped-wedge design is an ideal design to evaluate an intervention on a population level, where there are implementation resource constraints. This design is also useful where there are ethical or community concerns that all participating sites should eventually get the intervention. As a crossover design, it also controls for confounding and site-level differences because each site is observed before and after the intervention. Therefore, changes within the wider health system over time can be observed, given data is available from multiple pre-intervention and intervention sites at various points in time [15].

The intervention will be implemented at four to five LTC facilities each quarter (every 3 months), with all facilities having implemented the intervention in 30 months. The pre-implementation phase will take place over 1 month. During the pre-implementation phase the researchers contact the participating sites, meet with site leaders and staff, conduct a barriers to implementation assessment, provide the overarching rationale for the implementation program and outline the plan for implementation (i.e., setting an implementation workshop and determining what additional resources are required). Baseline data with the OPTIC tool and chart abstractions will be done prior to the intervention, with implementation occurring over the subsequent 2 months. The intervention will then become an expected standard care practice at the facility, and thus this will be considered the post-implementation phase.

The order of implementation will be randomized using random number generation to reduce bias, where the unit of randomization is the LTC facility. LTC facilities with the same owner-operator will be randomized to the same implementation period, given that these facilities often share staff. Until the pathway is implemented at a LTC facility, facilities will act as controls for the purposes of analysis.

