### Evaluation plan

The evaluation framework will use a mixed-methods approach, where quantitative and qualitative data collection will occur using a concurrent dominant design. Mixed methods research involves collecting, analyzing, and interpreting quantitative and qualitative data in a single study that investigates the same underlying phenomenon [29]. Mixed methods research is useful for studying complex health issues such as motivations, attitudes, perceptions, beliefs, and values that underlie health behaviours within social, economic, organizational, and political contexts that cannot be captured by either quantitative or qualitative designs alone [30]. The primary outcome will be the change in the rate of transfers to ED from LTC facilities. Specifically, we will compare differences in the rate of transfers per 1000 resident days. This will be used to track the effectiveness of the intervention at the LTC sites (i.e., changes in the rate of transfer before and after the intervention). Data on all LTC-ED transfers are currently collected as part of administrative data by Alberta Health Service Analytics. Over the 30-month study period, our current rate of ED transfers would result in over 8000 LTC-ED transfers from patients within the 38 participating Calgary LTC facilities. After we account for the stepped-wedge design effects and plausible levels of over-dispersion, this will provide 80% power to detect a 15% reduction in the rate of LTC-ED transfers (primary outcome) [15, 31–33].

Secondary outcomes, using data obtained from administrative databases, will include the change in the rate of LTC admissions to hospital per 1000 resident days and the proportion of LTC residents cared for in their LTC facilities through community paramedicine post-pathway implementation. Consenting residents will also evaluate community paramedicine and ED care episodes by completing a modified version of the OPTICS (Older Persons Transition in Care Success; see Additional file 1) Success tool, within 2 days of a community paramedic visit or an emergency department visit that did not result in a hospital admission [31]. The OPTICS tool has been used and validated in previous studies [34, 37].

The appropriateness of the pathway triage decision will be assessed using a random

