### Analysis plan

#### Quantitative analysis

The rate of transfers to ED from LTC facilities will be expressed as the number of ED transfers per 1000 resident days within each three-month cluster period. For our primary outcome, we will use a negative-binomial generalized linear mixed effects model. This model will have random intercepts for sites, an indicator variable for treatment mode in each cluster at each period and time, and fixed effects for time [15]. This model will account for Poisson over-dispersion, as well as correlations among observations within sites [31–33]. As a secondary analysis, we will use an individual-level analysis to determine whether the impact of the intervention depends on available patient-level factors (such as sex) and in a multilevel mixed-effects model with patient-level and site level effects. Generalized linear mixed-effects models will be used to assess a time by intervention effect on other outcomes using the link functions required to meet model assumptions [40].

Descriptive statistics will be used to determine the proportion of LTC residents cared for in their LTC facilities by the community paramedicine program, using the new LTC-ED care and referral pathway. This will be expressed as the number of Mobile Integrated Health (MIH) community paramedic LTC visits per total RAAPID calls from LTC. Descriptive statistics will also be used to present data on the appropriateness and safety of the pathway triage decision. The median and interquartile range will be calculated for the modified OPTICS tool scores for each of the three groups: pre-intervention ED transfer, post-intervention ED transfers, and post-intervention community paramedicine visits. Time series analysis will be used to compare the different groups.

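### Facilities are allocated to waves by owner-operator block, but the primary model has only site random intercepts, so any positive owner-by-quarter correlation makes its standard error too small

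*Protocol article*

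**What the plan says.** All references are to the protocol article.

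- **Methods, Study design.** The order of implementation is random, "where the unit of randomization is the LTC facility". The next sentence restricts this: "LTC facilities with the same owner-operator will be randomized to the same implementation period, given that these facilities often share staff".
- **Size and timing (same section).** "By the end of the study, all 38 participating LTC facilities will have received the intervention". On pace, with the last figure in months: "The intervention will be implemented at four to five LTC facilities each quarter (every 3 months), with all facilities having implemented the intervention in 30".
- **Analysis plan, Quantitative analysis.** The primary analysis is a negative-binomial mixed model of transfers per three-month period with fixed time effects. On its random part: "This model will have random intercepts for sites". The section says the model deals with over-dispersion and with correlation within sites. It names no owner-operator level.
- **Evaluation plan.** Over 30 months, "our current rate of ED transfers would result in over 8000 LTC-ED transfers". On power: "After we account for the stepped-wedge design effects and plausible levels of over-dispersion, this will provide 80% power to detect a 15% reduction". No alpha, dispersion, correlation or number of owners is given.

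**The concern.** The two sentences on randomisation do not describe the same unit. If an owner runs several participating sites, those sites move from control to intervention together, as one draw.

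The protocol's reason for the rule, shared staff, is also a reason to expect dependence. Staff deliver the intervention through education of aides and nurses, the early-warning tool and the condition cards. An owner-wide change in staffing or policy in one quarter would move the transfer rates of all that owner's sites together, and those sites always have the same treatment status. A site intercept removes stable differences between sites but cannot represent a shock shared by several sites in one quarter. The model would count such a shock as several independent observations.

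At stake are the primary confidence interval and p-value, which could be too optimistic, and a power figure that could be too favourable.

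**Working it through.** **Inputs from the protocol article.** 38 facilities; 30 months in three-month periods, so 10 quarters; about 8000 transfers, so 8000 / (38 × 10) = 21.05 per facility-quarter; rate ratio 0.85; power 80%.

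**Assumed, because not stated.** Two-sided alpha 0.05. First quarter all control, then nine waves (7 × 4 + 2 × 5 = 38). Site-intercept SD 0.3 (variance 0.09) on the log scale. Number and sizes of owner blocks varied. Share of extra-Poisson variance common to one owner's sites in a quarter: 10%, 25% or 50%.

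**Step 1: the stated 80%.** It cannot be reproduced, because the dispersion used is not given. For 80% power the required standard error of the log rate ratio is

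|ln 0.85| / (1.960 + 0.842) = 0.1625 / 2.802 = 0.058.

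I used the generalised least squares variance with fixed period effects, a site intercept and cell variance 1/21.05 + φ. A standard error of 0.058 corresponds to φ = 0.067. The 80% is therefore attainable with independent facilities, but it depends strongly on dispersion. Across layouts of 8 to 10 waves and site variances of 0.05 to 0.2, power is 98–99% with no over-dispersion and 39–50% at dispersion 0.25.

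**Step 2: same estimator, owner-quarter correlation added.** Keep the site-intercept estimator and compute its true (sandwich) variance when a share of φ is common to same-owner sites in a quarter. Then:

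- actual type I error = 2 × [1 − Φ(1.96 × SE_model / SE_true)], with SE_model = 0.058
- power of a test using the correct standard error = Φ(0.1625 / SE_true − 1.96)

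Example, sites in pairs with 25% shared: SE_true = 0.0616, ratio 1.062. Type I error = 2 × [1 − Φ(1.96 / 1.062)] = 6.5%. Power = Φ(0.1625 / 0.0616 − 1.96) = Φ(0.68) = 75%.

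| Owner layout (assumed) | SE_true at 10 / 25 / 50% shared | Type I error | Power |
|---|---|---|---|
| Every owner one site (38 blocks) | 0.058 throughout | 5.0% | 80% |
| Five two-site owners, rest single (33 blocks) | 0.0584 / 0.0590 / 0.0601 | 5.2 / 5.4 / 5.8% | 79 / 79 / 77% |
| Nearly all in pairs (20 blocks) | 0.0595 / 0.0616 / 0.0650 | 5.6 / 6.5 / 8.0% | 78 / 75 / 71% |
| Up to three per owner (18 blocks) | 0.0604 / 0.0637 / 0.0689 | 6.0 / 7.4 / 9.9% | 77 / 72 / 66% |
| One owner per wave (9 blocks) | 0.0629 / 0.0696 / 0.0795 | 7.1 / 10.2 / 15.3% | 73 / 65 / 53% |

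**Step 3: which kind of owner effect matters.** If the owner effect is constant over time, with 25–50% of the site variance shared, the standard error rises by only 1–2% with pairs and 3–6% with nine blocks, because the site intercept absorbs most of it. The larger losses need shocks shared by an owner's sites in the same quarter.

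**The case against.** The strongest reply is that the harm is conditional. It needs a material number of the 38 facilities to share an owner, and positive residual correlation between them after site intercepts and period effects. The article gives neither quantity. Shared staff makes the correlation plausible without sizing it, and with a few two-site owners the loss is minor. This stands, and it is why the result is a range that starts at no loss.

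Four stronger readings are tempting, and the document does not support them.

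- *The standard error is certainly too small and type I error certainly above 5%.* Both follow only if multi-site owners and positive owner-by-quarter correlation are present.
- *The power calculation treated the 38 facilities as independent.* The article gives 38 only as the source of the transfers and does not show the calculation. That owner clustering was left out is an inference from the two allowances listed.
- *Owner-specific responses to the pathway inflate type I error.* They do not when no facility has an effect. Region-wide shocks are likewise taken up by the fixed time effects.
- *The block rule conflicts with four to five facilities per quarter.* It would only if some owner had more than five participating sites, and nothing in the article shows that.

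It could also be said that such detail belongs in a fuller plan. That holds for the power inputs. It does not hold for the primary model, whose random effects the article fixes, or for the two sentences on the unit of randomisation, which disagree as written.

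**Conclusion.** The concern holds in conditional form. The named unit of randomisation is not the unit allocated wherever an owner has several sites, and the stated primary model has no term for that level. Under any positive owner-by-quarter correlation the model's standard error is too small, and a valid analysis has less power than one with independent facilities.

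The size runs from nothing (one site per owner) through a small effect (five two-site owners) to a serious one (one owner per wave, the extreme case). These figures rest on the assumed nine-wave layout, site SD 0.3, two-sided 5% alpha, an extra-Poisson variance back-solved from the stated 80%, and 10–50% of it being shared. The direction does not depend on those choices; the size does. Confidence is moderate. It should be fixed before analysis, but the documents do not show that the primary result will be invalid.

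**What to change.** 1. In Study design, state that the owner-operator block is the randomised unit, and report the number and sizes of the blocks.
2. Keep the site intercept and make the primary inference respect the block. One route is an owner-by-period random effect with owner-clustered, small-sample-corrected standard errors. Another is a permutation test that re-randomises owner blocks to waves. A time-constant owner intercept alone is not enough, because it does not represent shocks shared within a quarter. Where most owners have one site, the owner-by-period term is hard to separate from the negative-binomial dispersion, which favours the permutation route.
3. Restate the power from the actual blocks, giving alpha, dispersion and the assumed within-owner correlation. If owner clustering was already allowed for, say so.

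The cost is revised wording and a recalculated power figure; no new data are needed. The downside is a possibly wider confidence interval and a less favourable power statement.

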### Implementation process and strategy

This is an integrated knowledge translation project informed by the knowledge to action (KTA) cycle [16]. Specifically, we identified an evidence-informed solution to address a care gap and have engaged with relevant stakeholders. We will implement this change initiative, considering both local LTC context and barriers to implementation. The facility implementation can be modified to address these identified barriers, without altering the pathway (i.e., intervention) or the outcomes analyzed. All LTC facilities involved in the project will receive the same package and training. As to how each facility adopts the intervention is based on the discretion of the facility with the implementation team working to support and tailor implementation to each facilities’ needs and help overcome barriers identified in each facilities’ barrier assessment.

A survey to assess barriers will be completed by the staff within each LTC facility during the pre-implementation phase. By identifying potential local barriers to implementation up front, each facility can develop a local package of implementation strategies that addresses their unique implementation barriers. This barrier survey was developed using the Theoretical Domains Framework (TDF) [17–19] and successfully piloted in two continuing care facilities in Calgary. The Behaviour Change Wheel [17] which includes nine intervention elements that can be mapped to the identified barriers among 14 behaviour change domains within the TDF, will be used to help guide the implementation strategies within each LTC facility. Although the exact implementation strategies will be adapted for the local context within each facility, the implementation will include: i) education for LTC health care aids (HCAs) and nursing staff; ii) notifications sent to attending physicians in LTC; iii) site champions; iv) use of printed materials developed with support of the resident and family project team members and; v) focus on informing LTC residents and their families of this change in care processes.

A central implementation coach will provide support to the LTC staff to develop their local implementation plan and then help them to execute the plan, as well as providing consultative support to facilities post-implementation [20]. Each LTC facility will be encouraged and supported to develop an implementation team, consisting of key stakeholders such as managers, nurse educators, front-line staff, and residents/family members.

Utilizing the Patient-Centered Outcomes Research Institute (PCORI) model of patient engagement [21–23], we recruited residents and family members to participate as members of the project team, through the formation of a Resident and Family Advisory committee (RFAC). In alignment with PCORI, members of the RFAC received training opportunities to more fully engage in this research project. The RFAC will be involved in several aspects of implementation and evaluation including oversight of the PRIHS intervention and ensuring that it reflects the needs of LTC residents and family members, direct involvement in designing both interview and focus group questions, acting as liaisons’ between the project and local RFAC groups at LTC facilities, providing leadership and oversight to a communications working group tasked with developing educational materials for residents and family members, and assisting in implementation by delivering their own experiences with having family members transferred from LTC to ED while helping to inform and engage the residents and family members from within the LTC facilities affected by this change in clinical practice.

